## Abstract

**Abstract:**

**Introduction:**

Access to care varies by sociodemographic group, with some groups facing higher barriers to care than others. This study will use novel methods to explore barriers and potential solutions as perceived by members of the population groups who are least able to access care. We aim to use rapid yet robust mixed methods that allow us to identify generalisable findings within each programme and testable service modifications to improve equitable access to care; delivering non-tokenistic findings within a matter of weeks.

**Methods and analysis:**

This is a multiphased exploratory sequential mixed methods study. We will use the same approach in four different screening programmes, in Botswana, India, Kenya and Nepal. First, we will conduct interviews with people purposively selected from the sociodemographic subgroups with the lowest odds of accessing care within each programme. We will explore their perceptions of barriers and potential service modifications that could boost attendance at eye clinics among people from these ‘left-behind’ groups. We will use a deductive analytic matrix to facilitate the rapid analysis of qualitative data. Space will be made for the inductive identification of themes that are not necessarily captured in the framework. Sample size will be determined by thematic saturation. Next, we will conduct a survey with a representative sample of non-attenders from the same left-behind groups, asking them to rank each suggested service modification by likely impact. Finally, we will convene a multistakeholder workshop to assess each service modification based on ranking, likely impact, feasibility, cost and potential risks. The most promising service modifications will be implemented and evaluated in a follow-on randomised controlled trial, the methods for which will be reported elsewhere.

**Ethics and dissemination:**

This project has been approved by independent research ethics committees in Botswana, Kenya, India, Nepal and the UK. We will disseminate our findings through local community advisory boards, national eye screening meetings, in peer-reviewed journals and at conferences.

STRENGTHS AND LIMITATIONS OF THIS STUDYWe have developed a rapid qualitative approach that is designed to deliver rich and robust data with speed and relatively low costs.By using mixed methods, we are able to move from rich data to statistically generalisable findings that can be implemented across individual programmes.Our project is embedded within real-world programmes and will deliver actionable intelligence directly to policymakers, programme funders and programme implementers.Our proposed methodology places the experience and perspectives of ‘left-behind’ groups at the very centre of programmatic quality improvement.Our approach is based on a scoping review of rapid methods, however it is yet to be tested and validated.

## Introduction

### Equitable access to care

 Universal health coverage (UHC) has been described as the core of the health-related Sustainable Development Goals.^1 2^ As such, boosting access to community-based services has become an important global health priority.^3 4^ Inequitable access is a ubiquitous problem, with minoritised groups often facing the highest barriers to care.^5 6^ The ‘central transformative promise’ of the Sustainable Development Goals is to ‘leave no one behind and reach the furthest behind first’.^7^ Acknowledging that different groups face different barriers in different settings, WHO encourages health programme managers to routinely perform equity analyses in order to identify which specific groups are being left behind in each setting.^8^

Our group has produced guidance on how to perform these equity analyses using case studies from the field of eye care.^9^ Studies from Nigeria, Sri Lanka, Kenya and work in press from India, Botswana and Nepal show that different groups are being left behind by different programmes, ranging from elderly female widows in Sri Lanka to young men in full-time employment in Kenya.^10 11^ Once these groups are identified, the next step is to identify the unique barriers they face and potential solutions to improve access to care. Ideally, this work would be conducted quickly enough to inform programmatic decision-making.

#### Whose perspective do we want to hear?

Across all health service research, efforts to understand and address barriers to access have disproportionately focused on eliciting the opinions and perspectives of ‘experts’ and service providers at the expense of affected people and communities.^12^ Grounding elicitation work in the experiences and perceptions of service users and non-attenders is important both for ethical reasons^12 13^ and because their perceptions often differ from those of service providers.^14 15^ While elicitation studies from the field of eye care have largely been alive to this fact, there are still major issues: the approaches used to explore people’s perceptions have been disproportionately based on the use of closed questions and surveys, or on undertheorised and poorly described qualitative methods.^14^,^20^

#### Quantitative versus qualitative approaches for exploring barriers and solutions

The literature on barriers to accessing eye care is dominated by findings from in-person surveys that have been bolted onto population-based screening studies. These commonly take the form of a single survey item where participants are asked to choose or rank reasons for non-attendance from a preselected list of options.^17^,^1919 21^ This is also the approach used in *Rapid Assessment of Avoidable Blindness* surveys—of which >300 have been conducted in >80 countries.^27^ In our review of the literature, we only found two studies that provided a rationale for the list of barriers that they present to participants: Marmamula *et al* asked participants in South India to rank 15 barriers that had been generated by previous focus group work.^28^ However, none of the focus group participants were intended service beneficiaries or people with lived experience of trying to access eye care (all were service providers, public health experts and researchers).^29^ Furthermore, while the people responding to the final survey all had some form of vision impairment, they had not necessarily ever been referred to a service, which may explain why ‘lack of felt need’ and ‘lack of awareness’ were the most frequently selected barriers. Sengo *et al* performed a literature review and interviewed 25 people in Mozambique with vision impairment to identify which barriers should be used in a wider survey.^30^ However, the exercise was inadequately described, and the authors do not provide any detail on how the qualitative data were analysed.

Almost all surveys use a familiar list of barriers that commonly recur in qualitative studies, including high costs, long distances, transport issues, low trust in service providers, perceptions of low service quality, communication challenges, fear, scheduling issues, low awareness of services on offer, lack of a chaperone and the perception that vision impairment is not a significant impediment to function.^14^,^1820 22^ The main limitation in using surveys with these preselected items is that other important factors may be at play in a given population, but it is impossible to ascertain what they are without using open questions.^33^ Methods to elicit these barriers do not have to be particularly sophisticated: even though Sengo *et al* appear to have used relatively basic qualitative methods, their study still uncovered novel and important barriers including overcrowding in the local hospital, self-medication and the use of spectacles bought on the street.^30^ Similarly, while the method outlined by Marmamula *et al* to interview 199 elderly non-attenders provided no reference to theory, no underlying framework and no detail on the analytical approach, the work proved vital to understanding local contextual issues, with two-thirds of respondents citing novel barriers including lack of family consent and the adverse impact of other health conditions.^34^ These factors would not have been elicited from participants through a standard survey.

When are *any data* better than *no data*? Poorly designed qualitative studies can lead researchers to the wrong and sometimes harmful conclusions, just as flying blind without any understanding of the issues faced by service users can lead managers to introduce well-meaning ‘improvements’ that carry negative unintended consequences. We would argue that using appropriate, theory-driven qualitative methods with a sensible sample and well-described methods is actually a very low threshold to clear and can add real value at low cost in settings where the alternative is not using any open questions at all.

#### Previous qualitative studies that have examined access to eye care

There is a paucity of studies that have used qualitative methods to explore barriers to care. Ahmad *et al* used an open-ended survey question and content analysis to identify barriers to accessing eye care among the general population in Karachi. Unsurprisingly, given the population included, low perceived need was a major reason for not seeking care, however issues around health beliefs and cultural attitudes were surfaced that represent important issues for local health teams to engage with.^35^ Zabeck *et al* used structured telephone interviews to explore barriers to access among 28 Americans who had become blind. Using a constant comparative approach they found that social support structures and personal readiness to change were important factors for some people, alongside familiar themes of geographic access and low trust in providers.^36^ Elam and Lee conducted content analysis on data from four focus groups with American community members at risk of not attending eye services. Issues around health insurance, racism, unfriendly service at the clinic and procrastination supplemented familiar themes of cost, trust and fear.^31^ Kulkarni *et al* conducted in-person interviews with transgender people and sex workers with vision impairment in Pune, India, followed by focus group discussions with service providers. Their interview topic guide used deductive (ie, pre-identified) themes to structure the questions, and made space ‘to identify previously unexplored domains’. It appears that the provider focus groups were conducted in parallel in order to triangulate findings from the interviews. This approach was also used in studies led by Owsley *et al* and Okoye *et al*; both triangulated interview data from the target population with the perspectives of service providers, and Okoye *et al* also engaged with policymakers.^14 15^

#### Which population should be sampled?

While most eye care studies that assess access have sampled participants from either the general population or the population of intended service beneficiaries, three studies have specifically engaged ‘non-attenders’ (we note that this term is not perfect as it implicitly places responsibility for access onto users rather than services). It is likely that those who have been diagnosed with an eye condition; referred and not managed to access those services will have greater insight on the barriers to access and potential solutions than members of the general population who do not have this lived experience. Chou *et al* used a survey with preselected items to elicit reasons for non-attendance,^20^ but Gower *et al* used semi-structured telephone interviews which enabled participants to cite barriers that the researchers might not have previously considered.^16^ Similarly, Marmamula *et al* used in-person semi-structured interviews to elicit reasons for low eye clinic access among elderly care home residents.^34^

#### Theory

Very few of the qualitative studies that we found grounded their analyses in theory or a conceptual framework. While there are many different conceptual frameworks on generic barriers to accessing services,^37^,^39^ we are not aware of any that have been developed for eye care beyond the Australia-focused tripartite division of ‘predisposing’, ‘enabling’ and ‘need’ characteristics described by Keefe *et al*.^40^ Despite the breadth of eye service utilisation studies that have been conducted in the past two decades, it seems that it is rare for quantitative or qualitative eye care studies to use theory to inform the design of data collection activities or guide interpretation of findings. Positively, unlike healthcare access research from other fields, approaches that are grounded in eliciting the views of people and communities (as opposed to ‘experts’) are the norm, but these disproportionately sample form the general target population, rather than those with lived experience of being unable to access care.

## Study aim

In this study, we aim to develop a rapid, theory-based, scientifically robust approach that can be used to elicit barriers to accessing care and potential solutions through engagement with ‘non-attenders’ from sociodemographic groups that experience the lowest overall access rates when referred from screening programmes. We intend to test this approach in four different eye screening programmes running in Botswana, India, Kenya and Nepal and then apply the findings within the same services with the ultimate aim of improving equitable access to care. Findings from one programme will not be applied to the others, although learning will be shared across sites.

## Objectives

In each individual screening programme, conduct interviews with people from the relevant left-behind groups who have not been able to access clinics (identified in previous equity analyses) to explore barriers and potential solutions.In each individual screening programme, conduct phone interviews with a representative sample of people from the relevant left-behind groups, asking them to rank each of the mooted solutions.In each individual screening programme, convene the programme funder, programme implementing team, community representatives and national eye care policymakers at a workshop to review the ranked solutions and select one or more for implementation and evaluation.

### Programme-specific requirements

The nature of the screening programmes imposes a methodologically challenging set of requirements. Given that some programmes screen entire regions in a matter of months, the approach that we use must be able to deliver service modifications rapidly enough to benefit a reasonable proportion of the remaining intended beneficiaries; ideally within 1–2 months. Next, rather than presenting participants with a preselected list of barriers and service modifications and then asking them which are most important, we want to use open questions that allow participants to use their own words to identify issues and approaches that the research team may not have necessarily considered. We recognise that coding and interpreting these responses requires time—however speed is a key objective to ensure feasibility when running at large scale on tight resources. Peek Vision - the social enterprise that provides the screening programme software - is keen for its programme partners to use any resultant methods that can improve referral uptake, but the cost of these research activities will ultimately be borne by programme funders and will likely be offset by a reduction in the total number of people screened. As such, there is considerable pressure to keep the overall costs as low as possible. A related constraint is that local teams will only have access to a small number of staff with basic research training. We note that the availability of experienced qualitative and mixed-methods health system researcher staff is low across many low- and middle-income countries.^41 42^ Next, as stated above, we want to base decisions on the experiences and perspective of those directly affected: people who have been identified with an eye need and referred, but who have not been able to access services. Furthermore, we aim to focus on the needs of the sociodemographic group with the worst access to care (‘reaching the furthest behind first’) so that any improvements disproportionately benefit these groups, thereby improving equity, in line with the principle of proportional universalism.^6 43^ Finally, despite being rapid, inexpensive, non-prescriptive, equitable and primarily conducted by non-experts, we are committed to using robust methods to deliver valid, non-tokenistic findings. This is vital in order to inform programmatic changes that stand a chance of meaningfully improving access rates (box 1).

Box 1Our improbable wish listWe want to develop a rapid elicitation tool that can:be largely conducted by non-experts, although with expert supervision;deliver a set of barriers and potential solutions within weeks-months, rather than months-years;use open questions rather than relying solely on a predefined list of response options;provide barriers and potential solutions that are generalisable;gather data from non-attenders from sociodemographic groups with the lowest attendance rates within each programme;be conducted relatively inexpensively;and is methodologically robust.

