## Approach

### Philosophical paradigm

Our aim requires methods that span the space between constructivist and positivist philosophical paradigms.^44^ While the task of seeking to understand perceptions of barriers and solutions is primarily phenomenological, we intend to generalise the findings (ie, make statistical inferences) and develop service modifications that will be applied across entire programmes within each country. To traverse this philosophical rift, we will use a pragmatist paradigm, originally advanced by Charles Sanders Peirce.^45 46^ Pragmatism holds that ‘truth’ is determined by practical application and consequences, and it is agnostic on the type of research techniques used as long as they answer the research question.^45 47^

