### Methodology

We require mixed methods that draw on the strengths of both qualitative and quantitative approaches to answer a multilayered question: what are the main barriers to accessing eye services in each location (ie, each individual screening programme in each of the four countries) and what can be done about them?

Qualitive methods deliver rich, descriptive data based on interviews, discussions and/or observations with a select number of participants who are often purposively chosen because of their specific characteristics. As such, the findings can be transferred to similar cases and contexts, but they are not intended to be generalisable. In contrast, quantitative methods deliver numerical data and—with representative sampling—are able to provide evidence for causality, generalisability and magnitude of effect.^55 56^

We will use an exploratory sequential mixed methods approach; starting with qualitative methods to explore non-attenders’ perceptions of the barriers and potential solutions in each setting. We will use the identified themes to develop a unique, user-derived list of potential service modifications within each screening programme. We will then use quantitative methods—a survey—to establish which of these are perceived to be the most impactful through engagement with a representative sample of non-attenders, effectively validating or ‘sense-checking’ the qualitative findings with a larger, representative group. The ranked suggestions for service improvements will then be taken to a multistakeholder workshop where the top-ranked solutions will be considered for implementation based on their likely impact, feasibility, cost and potential risks.

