### Survey

Once we have generated a list of potential solutions, we will perform a survey to rank these in terms of perceived impact. Again, this approach is programme specific. At no point are we applying findings from one programme to another. As stated above, we will have a complete list of every non-attender belonging to the sociodemographic group with the lowest overall attendance rate. We will administer a telephone survey to a representative sample of non-attenders from this group, excluding all of those who have already been interviewed. We will use a 95% CI, a 5% margin of error and a conservative assumption that the total population size is 1 million people (with the same characteristics as the most marginalised group). This renders a sample size of 384.

We will use computer-generated numbers to obtain a random sample of non-attenders to call. Data collectors will seek verbal audio recorded consent before reading through the full list of potential service modifications that arose from the interview stage. Respondents will be asked to rank each suggestion from 1 to 3 on a simple Likert scale:

It would make a big difference, that is, if we introduced this change then you or people like you would definitely attend.It would make a moderate difference, that is, it would greatly increase the chances, but it would not be enough by itself to guarantee attendance by itself.It might make a small difference, that is, it might help a few people, but the impact is likely to be minimal.

We will calculate the average score for each service modification and generate a ranked list. Workshop participants will review the ranked list and select the most promising service modification to implement and evaluate.

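### The article wants generalisable barriers and a survey check of the interview findings, but the survey as described scores only solutions, so the barriers rest on purposive interviews alone

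*Protocol article*

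**What the plan says.** **What is promised.** Box 1, under Programme-specific requirements, wants the method to "provide barriers and potential solutions that are generalisable". The Philosophical paradigm section mentions perceptions of both barriers and solutions, then states: "we intend to generalise the findings (ie, make statistical inferences". The Methodology section opens with a two-part question, of which the first part is "what are the main barriers to accessing eye services in each location". It describes the survey as "effectively validating or ‘sense-checking’ the qualitative findings with a larger, representative group".

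**What is done.** Of purposively sampled qualitative work, the Methodology section says that "the findings can be transferred to similar cases and contexts, but they are not intended to be generalisable". The only representative sample is the telephone survey of 384 people per programme, introduced in the Survey section with: "Once we have generated a list of potential solutions, we will perform a survey to rank these in terms of perceived impact". Data collectors obtain consent before "reading through the full list of potential service modifications that arose from the interview stage", and each item is scored 1 to 3. The second objective and the Use of findings section agree that only service modifications go forward to the survey, after clearly unfeasible ones have been removed. Barriers go from the interview matrix to the workshop, where stakeholders discuss which of them can realistically be addressed.

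**The concern.** The barrier half of the question has no representative data behind it. A claim about the main barriers in a programme, made at the level of statistical inference, needs some estimate of how common each barrier is in the left-behind group. The interviews are not designed to give that estimate, and the survey does not ask.

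The checking claim is also wider than the survey can support. A respondent who scores a fixed set of proposals can show that a listed proposal is widely or weakly supported. The same respondent cannot show that an unlisted proposal matters, because no route for naming one is described.

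Two things are at stake. The workshop, and later readers, may treat interview-based barriers as if they had been confirmed in a sample of 384. And a useful modification that nobody raised in the interviews has no described way into the ranking.

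**Working it through.** **1. The statements side by side**

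| Place in the article | Barriers | Solutions |
|---|---|---|
| Box 1 | to be generalisable | to be generalisable |
| Philosophical paradigm | among the findings to be generalised | among the findings to be generalised |
| Methodology, research question | asked for | asked for |
| Objective 1, interviews | explored | explored |
| Objective 2, Use of findings, Survey | not included | scored by the representative sample |
| Workshops | discussed, from interviews only | discussed, with survey scores |

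The barrier column contains a generalisability aim and no step that could deliver it.

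**2. The survey size, reproduced**

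Inputs from the Survey section: 95% confidence (z = 1.96), margin d = 0.05, population N = 1,000,000. The proportion is not stated; p = 0.5 is assumed.

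- n0 = z² p(1−p)/d² = 3.8415 × 0.25/0.0025 = 384.15
- n = n0/(1 + (n0 − 1)/N) = 384.15/(1 + 383.15/1,000,000) = 384.00

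The stated 384 is reproduced. It is a precision calculation for a single proportion, so it would serve a yes/no barrier item directly.

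**3. Precision for a barrier proportion**

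The half-width at p = 0.5 is 1.96 × √(0.25/n). For the interviews this is only an illustration, because it treats purposively chosen people as a simple random sample.

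| n | Source | 95% half-width | Exact 95% CI if half name it |
|---|---|---|---|
| 14 | interview minimum | 26.2 points | 23% to 77% (7/14) |
| 20 | interview budget | 21.9 points | 27% to 73% (10/20) |
| 384 | survey | 5.0 points | – |

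**4. Chance that an item is never raised**

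Under the same illustration, the probability is (1 − p)ⁿ.

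| Share who would raise it | n = 14 | n = 20 |
|---|---|---|
| 5% | 48.8% | 35.8% |
| 10% | 22.9% | 12.2% |
| 20% | 4.4% | 1.2% |

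**5. The stopping rule**

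The Recruitment and sampling section sets a base of 12 interviews, then stops after two in a row with nothing new. I simulated this rule 5,000 times per scenario, with 25 to 50 subthemes whose prevalences run from 50% down to 2–5%. Neither the number of subthemes nor their prevalences are in the documents.

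- Geometrically spaced prevalences (many rare subthemes): about 14% to 26% of subthemes are never heard.
- Linearly spaced prevalences: about 7% to 10%.
- Under either spacing, over 99% of the subthemes with prevalence of at least 20% are heard, and about 95% or more of those with at least 10%.

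The losses are mainly rare items.

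**The case against.** The strongest reply is that the operative text already confines the generalised part to solutions. Box 1 is titled a wish list. In the Methodology section, what the survey is to establish is which service modifications are seen as most impactful. The Use of findings section claims a generalisable level only for actions, and the Output section makes a selected modification the primary product. Workshop criteria are impact, cost, risk and feasibility, and barrier prevalence is not among them. This stands. It limits the damage to the barrier claims and the wording of the check, and leaves the ranking of listed solutions largely untouched. It does not remove the mismatch, because the Philosophical paradigm section and the research question speak of barriers outside the box.

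A reader might infer that the survey is the same closed checklist that the Introduction criticises. The documents do not support that. The criticism is aimed at lists with no stated rationale, or not drawn from intended beneficiaries; this list comes from open interviews with non-attenders of the same group. That is the exploratory sequential design the article names.

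A reader might also take 20 interviews as a ceiling, or conclude that up to a quarter of ideas will be lost. Twenty is a budget figure and interviews continue to saturation. The upper end of the simulated range depends on assumed prevalences weighted towards rare subthemes, and rare items are unlikely to become the top-ranked modification.

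Burden is a fair objection too. Survey respondents are unpaid, on grounds of low time and cognitive load, and the teams are small. A yes/no item for every barrier subtheme would be too much. Finally, the survey form is not shown, so the point rests on the survey as the article describes it. That description is consistent across the second objective, Use of findings and Survey.

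**Conclusion.** The point holds in a limited form. Generalisable barriers are a stated aim that the described design does not deliver, and the survey can sense-check only the solutions on its list. This follows from setting the sections against each other and does not depend on any simulation.

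The size, for illustration only and under random sampling, is a margin of 22 to 26 points for a barrier proportion near 50% at the planned interview numbers, against 5 points at 384. A solution that 10% would raise has a 12% to 23% chance of being missed. The simulated share of unheard subthemes, about 7% to 26%, rests on assumptions outside the documents.

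It would go too far to say that half of the study fails or that the ranked solutions are invalid. The primary output is a chosen modification, and the survey does bear on that choice.

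**What to change.** Preferred: on the same 384 calls, add two things.

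1. A short item on the main barriers from the interview matrix, for example yes/no for the few raised most often. Report each as a proportion with a 95% CI; the half-width would be at most about 5 points.
2. One closing open question on anything else that would have helped the person attend. Code the answers into the same matrix and report them to the workshop.

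The cost is slightly longer calls and the translation and coding of short answers. No extra respondents are needed. Study status reports that data collection had not begun in Botswana, India or Nepal when the manuscript was submitted, so the change was still practical there at that point.

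Alternative, at no cost: in Box 1, Philosophical paradigm and Methodology, limit the generalisability and validation claims to the ranked solutions, and describe the barriers as exploratory findings from the interviews.
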